## Abstract

**Background:**

Multiple sclerosis (MS) is a chronic, progressive, and neurodegenerative disease affecting more than 2.8 million people globally. Mobility impairments are among the most significant challenges faced by people with MS, leading to physical inactivity, deconditioning, and disability progression (for some, even irreversible disability). This negatively impacts mental health, social participation, and quality of life while placing a considerable economic burden on society. Exercise can improve mobility and mitigate disability progression, but facility-based options are often inaccessible, especially for those in remote areas. Telerehabilitation offers a promising alternative, but current systems are limited by complexity and hardware requirements.

**Objective:**

The PLATINUMS (Implementation of an Advanced Telerehabilitation Solution for People With Multiple Sclerosis) project proposes an AI-driven telerehabilitation system to deliver accessible, cost-effective, and home-based exercise therapy for people with MS.

**Methods:**

The PLATINUMS project begins with working package (WP) 1, focusing on obtaining ethical approval and recruiting staff. Following this, WP2 involves a 4-week system feasibility and usability study (n=40) to assess and refine the digital platform. WP3 comprises a validity study (n=60) to evaluate remote mobility tests via the system, such as the Short Physical Performance Battery (SPPB), functional reach, and sit-to-stand tests, to ensure their reliability for use in WP4, the feasibility multicenter randomized controlled trial (RCT). The 10-week multicenter feasibility RCT will be conducted in MS centers across Denmark, Ireland, Israel, and Italy, with 96 participants varying in disability levels. The primary objective is to evaluate the efficacy of the AI-powered telerehabilitation system on mobility outcomes compared to usual care. Finally, WP5 will assess the cost-effectiveness of the telerehabilitation system by analyzing implementation costs, adherence, and use of health care. The PLATINUMS project aims to revolutionize exercise therapy for people with MS by demonstrating the feasibility, validity, and preliminary efficacy of the AI-driven telerehabilitation system. This approach addresses barriers such as accessibility, privacy, and standardization while promoting patient and therapist acceptance.

**Results:**

Funding for the PLATINUMS project was obtained in February 2024. WP2 data collection began in April 2025 across 4 European sites. WP3 is scheduled to launch in July 2025, with WP4 (the feasibility RCT) planned for January 2026. Initial WP2 results are expected by October 2025, with first publications anticipated in mid-2026.

**Conclusions:**

The PLATINUMS project is expected to generate critical insights into the feasibility, usability, and preliminary efficacy of an AI-based telerehabilitation system for people with MS. By leveraging widely available technology and real-time feedback, the system addresses key barriers to traditional rehabilitation. Findings from this protocol may inform future large-scale trials and support the broader implementation of digital health solutions in neurological rehabilitation.

**International Registered Report Identifier (IRRID):**

PRR1-10.2196/75983

## Introduction

Multiple sclerosis (MS) is a chronic and progressive disease of the central nervous system that affects more than 2.8 million people worldwide (35.9 per 100,000 people) [1]. One of the most common problems reported by people with MS is impaired mobility, specifically the inability to walk safely and independently [2,3]. Approximately 85% to 90% of people with MS report difficulties with mobility during the disease course [4], and these difficulties can commence very early after onset [5,6]. Due to progression of the disease, most people with MS will eventually require a walking aid (ie, a cane or walker) [7], and in some more severe cases, mobility is possible only by using a wheelchair or scooter [8]. Decreased mobility is, in part, also caused by reductions in physical activity [9], likely mediated through deconditioning of different physiological systems (eg, the cardiorespiratory system) [10]. At some critical points, mobility is limited to such an extent that there is an irreversible disability, resulting in secondary health conditions that are difficult, if not impossible, to treat [11]. This progression of disability also impacts mental health, which further contributes to decreased social, recreational, and vocational participation in society and ultimately results in a poor quality of life [12]. The decrease in participation and work productivity, in combination with an increase in secondary health conditions and medical needs, significantly impacts the global economy worldwide [13,14]. Since MS is the leading cause of disability in young and middle-aged adults, maintaining mobility is essential. Therefore, measures to combat or reverse this downward spiral and progression of disability must be developed and implemented to reduce the burden of this disease.

Exercise can improve mobility and perhaps decrease the rate and extent of disability (ie, impaired physical function) in people with MS [15,16]. Exercise programs based in hospitals and clinical facilities, particularly among other people with MS or under the supervision of MS experts, may help people with MS participate in exercise or exercise at a higher, more intense level [17]. However, a lack of access to these programs, especially for those who live in remote areas where there are few options or where there are health care and medical facilities but no MS experts, may make it difficult to engage in facility-based exercise training programs [18-20]. The COVID-19 pandemic highlighted the need to find alternative solutions to increase exercise and physical activity in the population with MS. In a series of studies involving members of the present consortium, we reported that physical activity and exercise activities, especially at moderate and high intensities, decreased during the pandemic in people with MS [21,22]. Moreover, the research consortium has strongly concluded that to ensure the continuity of exercise training for people with MS during future pandemics, health care stakeholders should be highly encouraged to provide training via advanced remote technologies concurrently with professional guidance and support [23].

Telerehabilitation has excellent potential for providing accessible and cost-effective options for exercise in the home environment for people with MS, particularly if there is ongoing communication with knowledgeable exercise personnel who ensure that exercise is carried out safely and optimally (ie, required movements are performed correctly). However, only a few studies have tested the capability of telerehabilitation to increase exercise and physical activity participation in people with MS, with some encouraging results [24-26]. Nevertheless, despite the advantages associated with the use of telerehabilitation, several limitations still exist that prevent the use of this technology on a large scale. In particular, most commercially available solutions do not provide feedback when the patient does not perform the exercise correctly or require special hardware (eg, movement sensors) that can be hard to set up for nonexpert users [27].

In this project, we intend to implement cutting-edge artificial intelligence (AI) technology designed by WizeCare [28] for a home-based exercise therapy program for people with MS. One of the advantages of this system is its technical simplicity. The system requires only a mobile phone, tablet, or personal computer and has no need for additional third-party hardware. This feature is essential for people with MS with low digital literacy [29]. Moreover, the technology incorporates an AI algorithm that calculates the range of motion and movement speed based on acquired videos of the user performing a specific exercise, enabling real-time feedback and positive encouragement during practice. Lastly, the system includes over 800 exercise drills classified according to targeted body regions and aspects of treatment (ie, flexibility, strength, or coordination) that the therapist can customize to create a personalized exercise program according to each patient’s goals and needs. Notably, the telerehabilitation system has been implemented in numerous health care services with thousands of users (mainly in orthopedic rehabilitation) and has yielded encouraging results in conjunction with positive feedback from patients, physical therapists, and stakeholders. Nonetheless, it has never been systematically tested in the population with MS.

Therefore, our overall goal is to implement an innovative telerehabilitation exercise training system for people with MS by assessing its efficacy in improving mobility. For this primary aim, we propose a pilot multicenter randomized controlled trial (RCT) in established MS centers across the European Union community in Italy, Ireland, and Denmark, as well as in Israel, to establish trial feasibility and to compare exercise delivery via telehealth with usual care. Further innovative aims of the project include (1) assessing the impact of a telerehabilitation exercise training program on mood and quality of life; (2) validating a set of remote mobility clinical tests delivered via the telerehabilitation system to evaluate balance and functional mobility in people with MS; and (3) examining the cost-effectiveness and value of the telerehabilitation exercise intervention program for people with MS. This information is scarce in the treatment of people with MS.

Ultimately, the knowledge obtained from this research will be relevant not only for people with MS; it is expected to also be of great value in understanding the most helpful way to deliver the benefits of home-based exercise therapy to other vulnerable populations, including many older adults who may appear healthy but are not, and others with neurological impairments (eg, stroke or Parkinson disease).

## Methods

### Overview

Our main objective is to collect evidence to facilitate the implementation of an innovative AI telerehabilitation exercise training system in MS clinical practice. After the completion of working package (WP) 1, which focuses on obtaining ethical approval and recruiting staff, our first objective (WP2) will be to investigate the usability and feasibility of the WizeCare system in MS centers in 4 European countries, encompassing a range of people with MS with varying disabilities and demographics. The second objective (WP3) will be to develop and psychometrically test a range of mobility measures collected by the telehealth system. The third objective (WP4) will be to compare exercise delivered via telehealth with usual care. The primary outcome will be trial feasibility, with preliminary efficacy for mobility, mental health, social participation, and quality of life outcomes. The fourth objective (WP5) will be to conduct an economic evaluation of exercise program delivery via telehealth compared with in-person care. The final objective will be to work collaboratively with clinicians, policymakers, and people with MS and to widely disseminate the knowledge generated by this program to optimize implementation. Figure 1 presents the WPs of the PLATINUMS (Implementation of an Advanced Telerehabilitation Solution for People With Multiple Sclerosis) project, while Table 1 illustrates its expected timeframe.

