### Research and Innovation Questions

This innovative project will include 5 key research questions (RQs), which we propose will fill in the gaps in our current knowledge.

RQ1 (WP2) is as follows: In people with MS, what is the usability and feasibility of an advanced telerehabilitation system in facilitating remote exercise training? Qualitative and quantitative measures will be used to evaluate the usability and feasibility of the telerehabilitation system in 4 countries. Following necessary system upgrades and adaptations, findings will be incorporated into the feasibility multicenter RCT (WP4). Based on data from other patient populations, we hypothesize that the innovative telerehabilitation system will score highly for usability and feasibility among the participants with MS.

RQ2 (WP3) is as follows: In people with MS, are scores provided by clinical mobility tests obtained via tele-rehabilitation valid and reliable? Evidence for remote mobility evaluation does not currently exist for people with MS. We will evaluate 5 tests developed from commonly used clinical measures. We hypothesize that innovative remote mobility tests will demonstrate good-to-excellent validity and reliability.

RQ3 (WP4) is as follows: In people with MS, is a large multicenter RCT possible, and can it show preliminary efficacy of an individualized exercise program delivered via telerehabilitation to improve mobility compared with in-person physical therapy? An international pragmatic multicenter feasibility RCT will be conducted to compare the effectiveness of delivering the individual exercise program via telerehabilitation versus in person by a physiotherapist. We hypothesize that both exercise intervention programs will improve mobility in people with MS; however, nonsignificant differences in mobility outcome measures between groups (telerehabilitation vs usual care) will be demonstrated.

RQ4 (WP4) is as follows: In people with MS, does an individualized exercise program delivered via telerehabilitation have a comparable effect on mood and quality of life (QoL) compared with standard physical therapy (facility based)? This RQ will be answered in the planned international multicenter feasibility RCT, preceded by a feasibility and usability study. Consequently, our hypothesis is that mood and QoL will be improved in participants whose symptoms are significant at baseline.

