### Outcome Measures for the Feasibility Multicenter RCT

The outcome measures for WP4 will include the 30STS [36] (primary outcome), SPPB [37], 6-minute walk test (6MWT) [38], timed 25-foot walk test (T25FWT) [39], mini-BESTest (balance) [40], FRT [41], and a self-report questionnaire, the 12-item MS Walking Scale (MSWS-12) [42]. In accordance with the project’s secondary aims, we will examine the impact of the intervention programs on mood (ie, depression and anxiety with the State-Trait Anxiety Inventory [STAI] [43] and Quick Inventory of Depression Symptomology [QIDS] [44]), quality of life (EQ-5D-5L [45]) and the impact of MS (29-question Multiple Sclerosis Impact Scale; MSIS-29 [46]).

All outcome measures will be collected at baseline (at the initiation of the intervention program), and after the intervention period’s completion. Assessors (physical therapists) will be blinded to group allocation, and patient report outcomes will be collected using an online form. Other significant disease-related factors collected solely at baseline (together with demographic and relevant clinical information) will include perceived fatigue (Modified Fatigue Impact Scale; MFIS [47]) and cognition (Symbol Digit Modality Test; SDMT [48]). Additionally, we will collect baseline information on digital literacy, which may confound the intervention’s effectiveness. All outcome measures used for the study have been validated in people with MS and are recommended for rehabilitation and clinical trials.

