### Data Analysis and Statistical Plan

Each research question is addressed through specific outcome measures. For RQ1, usability and feasibility will be assessed via the TUQ, adherence rates, dropout rates, and stakeholder interviews, with qualitative data analyzed thematically. RQ2 involves psychometric evaluation of remote assessments (e.g., SPPB, STS, and TUG) using intraclass correlation coefficients for test-retest reliability and Pearson correlations to compare remote and in-person scores. RQ3 and RQ4 outcomes (eg, 30STS, MSWS-12, EQ-5D-5L, STAI, and QIDS) will be analyzed using linear mixed models to assess within- and between-group effects over time. The primary analysis will follow an intention-to-treat principle, including all randomized participants in the groups to which they were originally assigned, regardless of adherence to the intervention protocol. A per-protocol analysis may be conducted as a secondary exploratory analysis. Missing data will be addressed using multiple imputation, assuming data are missing at random, and sensitivity analyses will be performed to assess the robustness of results.

As part of RQ5, the study also incorporates a comprehensive economic evaluation of the telerehabilitation system, which complements the clinical analyses and addresses a critical gap in MS rehabilitation research. A cost-utility analysis will be conducted to compare the telerehabilitation intervention and usual care, using incremental cost-effectiveness ratios derived from health care service use data and EQ-5D-5L–based quality-adjusted life years. Cost data will include implementation, infrastructure, maintenance, training, support services, and any differences in health service use or patient-reported outcomes. These data will be collected alongside the RCT to ensure alignment between clinical effectiveness and economic impact.

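### The feasibility RCT (WP4) has two competing primaries, trial feasibility and 30STS/mobility efficacy, and the feasibility one has no designated WP4 outcome or analysis

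*Protocol article*

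**What the plan says.** The protocol article describes the primary of WP4 in several places.

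- **Methods, Overview**, directly after introducing WP4: "The primary outcome will be trial feasibility, with preliminary efficacy for mobility, mental health, social participation, and quality of life outcomes".
- **Outcome Measures for the Feasibility Multicenter RCT**: "The outcome measures for WP4 will include the 30STS [36] (primary outcome", followed by the other mobility tests, a walking questionnaire, and mood, quality-of-life and MS-impact scales.
- **Abstract, Methods**: "The primary objective is to evaluate the efficacy of the AI-powered telerehabilitation system on mobility outcomes compared to usual care".
- **Introduction**: efficacy in mobility is presented as the overall goal and primary aim, and the pilot RCT serving it is "to establish trial feasibility and to compare exercise delivery via telehealth with usual care".
- **Table 1**: the WP4 row is titled as an efficacy study.

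The research question for WP4, RQ3, has two parts: "is a large multicenter RCT possible, and can it show preliminary efficacy of an individualized exercise program delivered via telerehabilitation".

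Under Data Analysis and Statistical Plan, the feasibility measures go to the WP2 question: "For RQ1, usability and feasibility will be assessed via the TUQ, adherence rates, dropout rates, and stakeholder interviews". The RQ3 and RQ4 outcomes, with 30STS and patient-reported scales as examples, "will be analyzed using linear mixed models to assess within- and between-group effects over time".

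The sample size is 24 per country in four countries, 96 in total, taken from a cited rule of thumb for pilot trials.

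**The concern.** Two sections use the term primary outcome for the same trial and name different things. The analysis section then develops only one of them. It opens by saying that each research question is addressed through specific outcome measures, but in that mapping feasibility belongs to the earlier four-week usability study. The outcome that the Overview calls primary for the RCT has no measure in the WP4 outcome list and no analysis under RQ3.

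Two things are at stake. First, with both labels standing, the headline result can be settled after the data are seen: a favourable 30STS estimate could be reported as the primary result, or a weak one set aside in favour of feasibility. Second, the choice determines whether the design suits its purpose. A sample taken from a pilot rule suits estimation of feasibility. It was not derived from power on 30STS.

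A smaller mismatch sits in the same place: the Overview lists social participation among the preliminary efficacy domains, while the outcome section lists no instrument dedicated to it.

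**Working it through.** **1. The statements side by side**

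| Place | What is put first for WP4 |
|---|---|
| Methods, Overview | Trial feasibility (primary outcome) |
| Outcome Measures section | 30STS (primary outcome) |
| Abstract, Methods | Efficacy on mobility (primary objective) |
| Introduction | Efficacy on mobility (primary aim), with feasibility also to be established |
| Table 1 | Efficacy study |

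30STS is a mobility test and stands at the head of the mobility outcomes. It is naturally the measure of the mobility-efficacy objective. The five places therefore reduce to two positions: feasibility, or efficacy as measured by 30STS.

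**2. Tracing the feasibility primary through the document**

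- Question: the first part of RQ3 (WP4).
- Outcome list for WP4: no item labelled as feasibility.
- Analysis: feasibility, adherence and dropout are tied to RQ1 (WP2). RQ3 receives linear mixed models on clinical and patient-reported scores.
- Data collected in WP4 that could serve: adherence and satisfaction (task T4.5 in Table 1), platform data on adherence and compliance, and weekly diaries for all participants (both under Intervention and Comparators). None is designated as a feasibility outcome. Recruitment and retention are not named as WP4 outcomes.

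**3. Sample size**

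The plan's own figure reproduces: 24 × 4 = 96. The article gives no alpha, power, effect size, SD, allocation ratio or dropout rate for WP4, so no power calculation can be reproduced. The 24 rests on a cited source that is not available here.

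**4. What 96 delivers under each primary (illustration only)**

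*If 30STS is primary.* Assumptions not in the article: 1:1 allocation (48 per arm), two-sided 5%, 80% power, no dropout, no baseline adjustment.

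Normal approximation: d = (1.960 + 0.842) × √(2/48) = 2.802 × 0.2041 = 0.572 SD. The exact t-test calculation gives 0.578 SD. Power by the normal approximation is 31% at 0.3 SD and 69% at 0.5 SD.

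*If feasibility is primary.* Take retention near 80% as an assumed value:

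| Retained | 95% CI (Wilson) | 95% CI (Clopper-Pearson) |
|---|---|---|
| 77/96, all countries | 71.1% to 86.9% | 70.8% to 87.6% |
| 19/24, one country | 59.5% to 90.8% | 57.8% to 92.9% |

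These figures do not measure the contradiction. They show only that its resolution changes what the same sample can support.

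**The case against.** The strongest defence is that this is a condensed article about a feasibility trial, and most of what seems absent may sit in the full protocol or analysis plan. Much of that defence stands, and it rules out several stronger readings.

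- *Three rival primaries.* A reader might count feasibility, 30STS and mobility efficacy separately. The last two fit together as measure and objective, so the conflict is two-way.
- *No feasibility data in WP4.* The article plans adherence and satisfaction data, and the Discussion adds use tracking and documentation of technical problems. What is missing is their designation as the feasibility outcome.
- *No go/no-go rule, so RQ3 cannot be answered.* Progression thresholds are often left to the full protocol, and ethics applications for WP4 were still to be submitted. Their absence here is no finding. One can say only that the article names no WP4 outcome or analysis for the first part of RQ3.
- *The trial will be judged on an underpowered 30STS p-value.* No alpha or success rule is stated. The Discussion calls the trial exploratory, concedes that small but meaningful effects may be missed, and looks ahead to a fully powered RCT. Sizing a pilot by a pilot rule is not an error.
- *The power figure.* It depends on an allocation ratio and complete follow-up that the article does not state, and it ignores baseline information that a longitudinal mixed model could use.

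The defence does not reach the contradiction itself. The Overview and the outcome section give different answers to the same question, and the analysis section places the feasibility measures under another work package. A document not shown can say which statement is intended, but it cannot make both correct.

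**Conclusion.** The point holds in this form: the article is wrong as written on the WP4 primary. The Overview says feasibility. The outcome section says 30STS, and the abstract, the Introduction and Table 1 side with efficacy. In addition, the published mapping of questions to analyses leaves the first part of RQ3 without a designated WP4 outcome or analysis.

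This conclusion rests on the text alone and needs no numerical assumption. The illustrative figures (about 0.58 SD detectable with 48 per arm; a CI of about 71% to 87% around 77/96 retained) depend on the assumptions stated with them and indicate only why the choice matters. It should be settled before WP4 opens. The social-participation mismatch is secondary.

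**What to change.** 1. State one WP4 primary, identically, in the abstract, the Introduction, the Overview, Table 1 and the outcome section. Feasibility fits better, because the sample follows a pilot rule and the Discussion treats the trial as exploratory.
2. In the outcome section, designate the WP4 feasibility measures: recruitment, retention at 10 weeks, adherence and completeness of 30STS. Report each as an estimate with a 95% CI, with any progression criteria fixed before the RCT opens.
3. Under Data Analysis and Statistical Plan, link these measures to the first part of RQ3, and keep the mixed models for the second part and for RQ4.
4. Relabel 30STS as the key efficacy outcome, estimated with a 95% CI as preliminary efficacy.
5. Name an instrument, or an existing subscale, for social participation, or remove that domain from the Overview.

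Cost: mostly wording. Adherence data are already planned, and retention and 30STS completeness follow from the baseline and post-intervention assessments. Recruitment needs a simple log, which the article does not mention. The efficacy claim is reduced to preliminary, as the Discussion already implies. Since the WP4 ethics applications were described as still to come, the change can be made in those submissions, or by amendment if they have since been filed.
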